## Methods: participants, interventions, and outcomes

### Study setting {9}

The study will be carried out at the Acharya Vinoba Bhave Rural Hospital’s Obstetrics and Gynaecology Ward at the Datta Meghe Institute of Medical Sciences in Sawangi (Meghe), Wardha, Maharashtra, India. The Obstetrics and Gynaecology ward’s patients will undergo screening to determine their eligibility.

### Eligibility criteria {10}

The inclusion criteria consist:

Women from 20 to 40 years of age,Type of LSCS: emergency and elective,Individuals with any mode of conception,Primigravida or Multigravida,Individuals with written consent.

The exclusion criteria:Non-co-operative patients,History of chronic back pain unrelated to pregnancy,Vaginal delivery,Individuals with sleep disorders,Individuals on sleep medications (hypnotics),Cognitive impairment.

### Who will take informed consent? {26a}

The principal investigator (PI) will take the informed consent.

### Additional consent provisions for collection and use of participant data and biological specimens {26b}

Not applicable.

#### Rationale

The principal investigator will collect consent from the subjects; no additional consent is needed. This protocol does not involve biological specimens as part of the process.

## Interventions

### Explanation for the choice of comparators {6b}

Both Benson’s and Mitchell’s relaxation techniques are psychophysiological treatments that have been shown to lower stress, pain, and anxiety and also enhance sleep quality and overall health. However, there is a lack of comparison between these two techniques in LSCS subjects. Both techniques are non-pharmacological, easy, and safe to implement in LSCS subjects without any adverse effects.

### Intervention description {11a}

#### Conventional physiotherapy exercise

Patients who meet the inclusion criteria will be selected following ethical clearance from the Institutional Ethical Committee.

Pretreatment and post-treatment data will be recorded with the help of outcome measures. After dividing patients into two groups, each group A and B will receive Mitchell’s relaxation and Benson’s relaxation, respectively, for 30 min along with breathing exercises; followed by this, patients will receive interventions 5 days a week. This relaxation would be given with conventional physiotherapy exercises in both groups. Intervention will be given on POD-2 after LSCS in both the groups A and group B.

**Table Tabb:** 

Sr no.	Intervention	Procedure
1	Thoracic expansion exercise	Larger than normal breaths are taken during inspiration, along with shoulder are expanded in flexion and during expiration shoulder are brought back to the neutral position
2	Kegel’s exercise	Tighten the pelvic floor muscle as you are holding the urine, maintain the contraction for 5 s, and then relax
3	Isometrics hamstrings	Bend the knee while lying supine in the bed, press the heel on the bed, and feel the tightness on the back of your thigh
4	Isometrics quadriceps	Press the knees on the bed, and the heel should raise the bed a little. Hold the contraction for 5 s and then relax
5	Ambulation	Walk with the proper abdominal binder to provide for the stitches

##### Group A

Subjects will receive 30 min Mitchell’s relaxation exercise per day, along with conventional physiotherapy exercises in both groups. Follow-up of the patient will be done daily. Diaphragmatic breathing exercises and a series of serial isotonic contractions aimed at reciprocal inhibition are both components of Mitchell’s physiological relaxation technique.

##### Group B

Benson’s relaxation will be administered to LSCS sufferers for 30 min. It is divided into five sections: (1) a calm environment: picking a spot devoid of disturbances; (2) it is crucial to assume a calming position, such as standing, sitting, sleeping, or walking; (3) appropriate acceptance: making sure that every muscle is relaxed, starting from the soles of the feet and working your way up to the face muscles; (4) concentration: maintaining awareness of breathing patterns and using the nose for inspiration and the mouth for expiration; (5) appropriate acceptance: keeping a calm demeanor. The techniques work by decreasing endogenous catecholamine levels and the activity of the sympathetic nervous system.

### Criteria for discontinuing or modifying allocated interventions {11b}

At any time, participants may request to stop or alter the intervention they have been assigned, or the investigator may decide that they should stop or alter the intervention if they suffer any discomfort, an adverse event, or a worsening of their condition.

### Strategies to improve adherence to interventions {11c}

Education and demonstration of participants: At the beginning of the study, participants will get explicit written and verbal instructions along with examples of the designated physiotherapy exercises and relaxation techniques. This guarantees that participants comprehend the processes and their significance.Supervised sessions: To guarantee proper technique and promote participation, interventions will be given or overseen by a principal investigator while the participants are in the hospital.

### Relevant concomitant care permitted or prohibited during the trial {11d}

#### Permitted concomitant care

Standard LSCS nursing care according to the hospital.Conventional physiotherapy exercise according to the protocol in both groups.Regular medications that were prescribed to postpartum women.

#### Prohibited concomitant care

Any other relaxation techniques.Yoga, meditations, or physiotherapeutic modalities.Use of hypnotics.

### Provisions for post-trial care {30}

Not applicable.

#### Rationale

Both relaxation techniques are safe and non-invasive without adverse effects.

### Outcomes {12}

#### Primary outcomes

Visual analogue scale (VAS) is one instrument used to rate pain. It is a simple and widely used method in medicine to assess the degree of discomfort.Incontinence severity index (ISI) is a questionnaire that measures the severity of urinary incontinence. It is used to categorize incontinence as slight, moderate, severe, or very severe.

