**Methods:**

Forty-six LSCS subjects with pain, urine incontinence, sleep quality, and activities of daily life will participate in a comparative study that is a blinded (statistical) analysis. The participants will be divided into two groups following randomization: (1) Benson’s relaxation and (2) Mitchell’s relaxation, and both groups will receive exercises from conventional physiotherapy. Every group will go through the initial evaluation and a post-intervention assessment.

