### Sample size {14}

#### Sample size: calculation for comparing two means at pain severity using VAS

##### Formula used

The formula for calculating the sample size for comparing two means is:$$n\geq\left[\left(Z\_\left\{1-\alpha/2\right\}+Z\_\left\{1-\beta\right\}\right)^2\cdot\left(\upsigma_1{}^2+\upsigma_2{}^{2/r}\right)\right]/\left(\mu_2-\mu_1\right)^2$$where:*Z*_{1-*α*/2} is the *Z*-score corresponding to the two-sided significance level.*Z*_{1-*β*} is the *Z*-score corresponding to the desired power.σ_1_^2^ and σ_2_^2^ are the variances of the two groups.*r* is the ratio of the group sizes.(*μ*_2_—*μ*_1_) is the difference in means between the two groups.Alpha (*α*): 0.05 (significance level) = 1.96Beta (*β*): 0.2 (power = 1—*β* = 0.8) = 0.084Mean in group 1 (*μ*_1_): 7.916 (A s per reference article)Standard deviation in group 1 (σ_1_): 2.256Mean in group 2 (*μ*_2_): 5.983Standard deviation in group 2 (σ_2_): 2.327Ratio of group sizes (group 2/group 1): 1:1

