## Statistical methods

### Statistical methods for primary and secondary outcomes {20a}

#### Characteristic statistics

Frequencies and percentages will be used to summarize qualitative data, such as demographic factors.

The mean ± standard deviation will be used to express quantitative data, including ratings from the visual analogue scale, incontinence severity index, Pittsburgh Sleep Quality Index, and Barthel Index Scale.

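### Two unranked primary outcomes, VAS and ISI, with no success rule and a sample size that covers VAS only; power for ISI is unsupported, and eligibility does not require incontinence

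*Protocol article*

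**What the plan says.** Under Outcomes {12}, the protocol article gives two primary outcomes in one list. The first is pain: "Visual analogue scale (VAS) is one instrument used to rate pain". The second is urinary incontinence: "Incontinence severity index (ISI) is a questionnaire that measures the severity of urinary incontinence", with four grades from slight to very severe. Neither is put first, and no joint success rule is given. Objectives {7} sets the aim as finding which group improves more.

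Sample size {14} is built on pain only, as a "calculation for comparing two means at pain severity using VAS". It uses alpha 0.05, with a Z-score "corresponding to the two-sided significance level", and power 0.80, and arrives at 23 per group. No ISI effect, standard deviation or power appears anywhere.

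The abstract describes the participants this way: "Forty-six LSCS subjects with pain, urine incontinence, sleep quality, and activities of daily life will participate". The inclusion list in Eligibility criteria {10} opens with "Women from 20 to 40 years of age,Type of LSCS: emergency and elective" and goes on to mode of conception, parity and consent. Nothing in the inclusion or exclusion list asks for incontinence or a minimum ISI score.

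Statistical methods {20a} treats all four instruments alike: "The mean ± standard deviation will be used to express quantitative data, including ratings from the visual analogue scale, incontinence severity index" and the two secondary scales. Groups are then compared by an independent t-test, or by Mann–Whitney if the data are not normal.

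**The concern.** With two primary outcomes and no rule, the protocol does not say what result answers its question. If VAS favours one technique and ISI shows nothing, or favours the other, any of several conclusions could be drawn after the data are seen. A single nominally significant result could be presented as success.

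The second issue is ISI itself. It has primary status, but the 46 women were not chosen to give it any particular power. The grades in the outcome description apply to women who leak. Since entry does not require leakage, an unknown share of participants may have nothing to grade and little or no room to improve. A non-significant ISI result could then be published as the two techniques being equal for continence, when the trial had little chance of showing a difference.

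**Working it through.** **Inputs from Sample size {14}.** Means 7.916 and 5.983 (difference 1.933), SDs 2.256 and 2.327, allocation 1:1, two-sided alpha 0.05, power 0.80.

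**1. The stated VAS figure.** n per arm = (1.960 + 0.842)² × (2.256² + 2.327²) / 1.933² = 22.07, rounded up to 23, so 46 in total. This reproduces. (The printed power quantile of 0.084 is a slip: used literally it gives 11.7, not 23.) The pooled SD is √((2.256² + 2.327²)/2) = 2.292, so the standardised difference is 1.933/2.292 = 0.843. Power at 23 per arm is 81.6% by the normal formula and 79.9% by the exact t-test.

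**2. If either primary can count as success, each at 0.05.** Independent outcomes: 1 − 0.95² = 9.75%. With bivariate normal test statistics: 9.1% at correlation 0.5 and 7.0% at 0.9. Splitting alpha to 0.025 each would restore 5%, but VAS power at 23 per arm would drop to 73.2% (t-test 70.4%). Regaining 80% would take 27 per arm (54 in total) by the normal formula, or 29 per arm (58) by the t-test.

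**3. If both must succeed, each at 0.05.** Alpha is not inflated. Assume that ISI has the same standardised effect as VAS, 0.843. Each test statistic then has mean 0.843 × √(23/2) = 2.86, and joint power is 0.816² = 66.6% at correlation 0, 70.9% at 0.5 and 76.8% at 0.9 (normal approximation). All are below 80%.

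**4. ISI at 23 per arm if every woman contributes.** The smallest standardised difference with 80% power is (1.960 + 0.842) × √(2/23) = 0.83. Power is 40% at a difference of 0.5 and 17% at 0.3.

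**5. ISI when some women are continent.** The documents give no incontinent share f and no ISI effect. I assume an effect of 0.843 SD among incontinent women only.

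- *All women analysed, effect diluted to f × 0.843, SD unchanged.* Power = Φ(2.86f − 1.96).
- *Incontinent women only.* Power = Φ(2.86√f − 1.96).

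| Assumed share f | All women, diluted | Incontinent only |
|---|---|---|
| 100% | 82% | 82% |
| 75% | 57% | 70% |
| 50% | 30% | 53% |
| 30% | 14% | 35% |

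A simulated Mann–Whitney test on all women is closer to the plan. I used five equally likely severity levels, the same 0.843-SD shift and f = 60%. Power is about 15% if a leaking woman's score can never fall to the no-leakage value, and about 31% to 34% if it can. The dilution formula at the same share gives Φ(1.716 − 1.96) = 40%. Share, effect and scoring all move the answer, but every version falls well below 80%.

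**The case against.** The strongest reply is that the printed numbers are right for what they cover. A reader might infer that the protocol's stated error rate or ISI power is false. The documents do not support that: they state no family-wise error and no ISI power, and the alpha, power and sample size given for VAS reproduce.

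A reader might also infer that the false-positive rate is nearly doubled. That holds only if success on either outcome suffices, which the protocol never says. Alpha 0.05 is printed only in the sample-size section, and a multiplicity procedure could sit in an analysis plan that is not shown. This stands, so the absence of such a procedure is not the point here. What the article itself fixes are two equal primaries and sizing on one of them. No later analysis plan can make 46 women adequate for an outcome that was not sized.

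A third tempting reading is that ISI is almost uninformative. Very low power figures depend partly on a scoring choice that prevents a woman who becomes dry from scoring as dry. Allowing that roughly doubles power at a 60% share. The range is what can be defended, not its lower end.

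Finally, the plan does not commit ISI to a t-test. Mann–Whitney is already provided for non-normal data, and mean ± SD is a descriptive summary. The remaining point about ISI reporting is small: a mean does not show how many women had no leakage.

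**Conclusion.** The concern holds in this limited form. The primary outcomes are unranked, no success rule is given, and the stated 80% power belongs to VAS alone. Under an either-outcome reading, family-wise error is about 7% to 10%, depending on the correlation between the outcomes. Under a both-required reading, error is controlled but joint power is about 67% to 77%, and that assumes an ISI effect as large as the VAS effect with every woman contributing. Neither reading gives 5% error together with 80% power.

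Power for ISI is unsupported rather than misstated. It falls steeply as the share of continent women rises, and its exact value cannot be fixed from the documents, because the share, effect and scoring are not given. The abstract and the eligibility list disagree on whether participants have incontinence, and the documents do not settle which is meant.

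**What to change.** 1. In Outcomes {12}, name VAS at week 4 as the primary outcome that carries the stated 80% power. Place ISI second, tested at two-sided 0.05 only if VAS is significant. This fixed sequence holds overall error at 5% for the two outcomes and leaves VAS at full alpha.
2. In Sample size {14}, say that the 80% does not cover ISI. Add that a non-significant ISI result will not be read as evidence of no difference.
3. In Statistical methods {20a}, commit ISI to the Mann–Whitney comparison already allowed there, and report counts per ISI category, including no leakage, by arm.
4. Reconcile the abstract with Eligibility criteria {10} on whether participants must have incontinence.

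The cost is a change to the protocol and registry text, and ISI gives up equal primary status, which is a real change of emphasis for a trial that aims at both pain and continence. No patients, visits or procedures are added. If the investigators want ISI to remain an equal primary, they should state the success rule and recompute the sample size with a justified ISI effect and incontinent share.

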#### Secondary outcomes

Pittsburgh Sleep Quality Index (PSQI) evaluates that the sleep quality is the goal. Respondents are asked how often they experienced particular sleep problems in addition to rating the quality of their sleep.Barthel Index Scale was used to evaluate scale independence. The overall score is between zero and one hundred points. Functional independence increases with a higher score [15].

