## Introduction

### Background and rationale {6a}

The rate of cesarean sections has dramatically increased globally in recent years. Two types of cesarean section are performed: elective and emergency cesarean section [1]. Women undergo a number of physiological, psychological, and social changes during the postpartum phase [2]. These changes result in a number of issues that impact women’s daily lives. Following a cesarean section, women seem to be more susceptible to sleep disturbances. This discrepancy is particularly noticeable in late pregnancy and the early postpartum period, which has been identified as a time of vulnerability to sleep problems [3]. A loss of bladder control known as urinary incontinence can range from a minor leak of pee following coughing, sneezing, or laughing to an absolute inability to control urination. Urinary incontinence is most common in women during pregnancy and after giving birth [4]. One of the most prevalent issues in the postpartum phase is back discomfort. Seven out of ten women who give birth have back pain, which is more than 70% of cases, according to statistical evidence. Obesity, poor posture, sitting, walking, and standing are all associated with postpartum back pain. According to the study’s findings, post-anesthesia back discomfort can be reduced by practicing posture correction, yoga, meditation, lumbar support, rest, and massage [5].

Therapeutic exercises that help reduce stress and anxiety both mentally and physically are known as relaxation techniques [6]. Relaxation techniques can also be used as adjunctive therapies in a range of healthcare settings to treat patients with a variety of diseases, mostly but not exclusively stress, anxiety, depression, and pain [7]. Psychophysiological therapies such as relaxation techniques reduce stress by encouraging mental and physical relaxation [8]. These methods effectively lessen pain and anxiety and are frequently used in physiotherapy [9]. A clear description of therapeutic relaxation appears challenging, even though relaxation is a widely recognized and frequently utilized term [10].

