## Data collection and management

### Plans for assessment and collection of outcomes {18a}

Baseline assessment: Before giving any intervention, data will be collected from subjects at the beginning of the first week.Intervention period: During the 4 weeks of the intervention, subjects will get both the relaxation technique (Benson’s and Mitchell’s), along with the conventional physiotherapy exercises.Post-intervention assessment: After the fourth week of intervention, right after the intervention period, data will be gathered once again.

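### If the PSQI recall period exceeds four days, most of the baseline window precedes delivery, so the paired within-arm PSQI change cannot be read as improvement in post-cesarean sleep

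*Protocol article*

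**What the plan says.** Four parts of the protocol article bear on this point.

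- **Instrument.** Under Secondary outcomes, the PSQI is described thus: "Respondents are asked how often they experienced particular sleep problems in addition to rating the quality of their sleep". The past-tense frequency question makes it a look-back form. No recall length is given.
- **Baseline day.** The section on assessment and collection of outcomes {18a} says: "Before giving any intervention, data will be collected from subjects at the beginning of the first week". The intervention description {11a} says: "Intervention will be given on POD-2 after LSCS in both the groups A and group B". Read as the starting day of a 4-week course, this puts baseline on or before POD-2.
- **Second assessment.** The same section {18a} says: "After the fourth week of intervention, right after the intervention period, data will be gathered once again".
- **Analysis.** The statistical methods {20a} plan a paired t-test or Wilcoxon signed-rank test of before against after within each arm. They also plan an independent t-test or Mann–Whitney test between arms. Whether the between-arm test uses week-4 scores or change scores is not said.

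The Background {6a} places sleep difficulty on both sides of delivery: "This discrepancy is particularly noticeable in late pregnancy and the early postpartum period".

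**The concern.** A paired before/after test is informative only if both readings describe the same kind of period, one untreated and one treated. Here the first reading is taken within two days of surgery on a form that looks backwards. Unless the look-back is very short, the woman is mostly reporting her sleep while pregnant. The second reading describes her sleep with a newborn, after the operation and during treatment. The end of pregnancy, the surgery and newborn care are then part of every woman's change score, whatever the relaxation technique did.

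What is at stake is how a significant within-arm result would be read. The Abstract expects sleep quality to improve after the cesarean and would carry demonstrated benefit into practice. The Discussion presents measurement before and after as a way to evaluate what the methods do for postpartum recovery. Section {20c} puts the weight of the analysis on pre/post comparisons. A change in PSQI could therefore be reported as improved post-cesarean sleep when its reference point is largely not post-cesarean.

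**Working it through.** The protocol gives no figure of its own on this point. Its one design calculation, 23 per group, is for VAS pain and does not enter here.

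**Inputs**

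- Day of baseline after delivery, d: at most 2, from {11a} and {18a} together.
- Length of treatment: 4 weeks, or 28 days, from {18a}.
- PSQI recall length, w days: not in the document, so it is treated as unknown and varied from 1 to 30 days.

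**Step 1: share of the baseline window before delivery**

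Share = max(0, w − d)/w.

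| Recall w (days) | Baseline on POD-2 | Baseline on POD-1 |
|---|---|---|
| 1 | 0% | 0% |
| 2 | 0% | 1/2 = 50% |
| 3 | 1/3 = 33% | 2/3 = 67% |
| 7 | 5/7 = 71% | 6/7 = 86% |
| 14 | 12/14 = 86% | 13/14 = 93% |
| 28 | 26/28 = 93% | 27/28 = 96% |
| 30 | 28/30 = 93% | 29/30 = 97% |

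**Step 2: where the baseline becomes mainly pre-delivery**

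(w − d)/w > 1/2 when w > 2d. With d = 2 this means any recall over 4 days. An earlier baseline lowers the threshold, so POD-2 is the case most favourable to the plan.

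**Step 3: the week-4 window**

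The second form is completed at about day 2 + 28 = 30 after delivery. Pre-delivery days in its window = max(0, w − 30), which is 0 for every w up to 30.

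**Step 4: consequence for each test**

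- *Within arm.* For w between 7 and 30 days, the paired test compares a window that is 71% to 93% pregnancy with one that is wholly postpartum. The change combines any treatment effect with the move from pregnancy to the postpartum state, and the two cannot be separated.
- *Between arms.* Allocation is random and both arms complete the same form at the same two times. The shift in window has the same expected contribution in each arm and cancels from the contrast, whether week-4 or change scores are used. The baseline is merely less useful as a reference point.

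**The case against.** **The recall length is an assumption.** This stands, and it makes the point conditional. A reader might infer that the baseline simply is a late-pregnancy measure. The document does not support that, because with a recall of 2 days or less completed on POD-2 the overlap is nil. A condensed article may also leave form instructions to the full protocol, so the missing recall length is not in itself a fault. The problem is the combination that the article does fix: a look-back form, a baseline by POD-2 and a paired test.

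**The same applies to the ISI.** A reader might infer this, since the ISI is a primary outcome completed on the same day and the Background says "Urinary incontinence is most common in women during pregnancy and after giving birth". The document describes it only in these terms: "Incontinence severity index (ISI) is a questionnaire that measures the severity of urinary incontinence", with severity categories. It gives no look-back wording and no recall period, so the argument does not extend to the ISI.

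**The Background does not say the two periods differ.** Correct. It groups them as "late pregnancy and the early postpartum period, which has been identified as a time of vulnerability to sleep problems". The document therefore gives neither the size nor the direction of any shift, and newborn care could make week-4 sleep worse. The point does not need a direction. It needs only that a mainly pre-delivery baseline is not a measure of post-cesarean sleep.

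**The objective is comparative, and the paired test makes no causal claim.** This is largely right. The Objectives {7} ask which arm improves more, and the between-arm test addresses that. A reader might infer that this comparison is compromised too; it is not, for the reason in step 4 of the working. But the Abstract and Discussion invite the before/after reading, so the risk of misinterpretation remains.

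**The Discussion already admits the lack of a control arm.** There is overlap: even with a one-day recall, within-arm change would mix in surgical recovery and newborn care. But an arm with conventional physiotherapy alone would not change which period the baseline covers, so the admitted limitation does not dispose of this one.

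**Conclusion.** The point holds for the PSQI and conditionally on its recall length. If the recall exceeds 4 days, more than half of the baseline window lies before delivery: 71% at 7 days, 86% at 14 and 93% at 28 to 30. The week-4 window is wholly postpartum for any recall up to about 30 days. The paired PSQI test then compares mainly late pregnancy with the postpartum weeks and is not evidence of improved post-cesarean sleep. At 3 days the overlap is 33%; at 2 days or less it is absent.

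This rests on reading POD-2 as the first treatment day, on baseline being completed that day or earlier, and on the PSQI being used as a look-back form, as the article describes it. The randomised comparison of the two techniques is unaffected, and so is the sample size.

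**What to change.** - Do not use the within-arm PSQI change as evidence of benefit. Either remove the PSQI from the paired tests in {20a}, or report its change descriptively only, labelled with the period the baseline covers.
- Base the PSQI conclusion on the between-arm comparison of week-4 scores, and say so in {20a}. This also settles whether week-4 or change scores are compared.
- State the PSQI recall period and use the same one at both visits. Shortening the recall at week 4 alone is not advised: it would alter an instrument the Discussion relies on as validated and would give the two visits different windows.

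The cost is a few lines in the outcome and analysis sections. Visits, treatment and the total of 46 women are unchanged. The one loss is the claim of within-arm PSQI improvement.
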